### Outcomes

#### Primary outcome measures

To evaluate transition readiness in PWEs and their caregivers, defined as the preparedness to manage healthcare needs, treatment adherence, and communication with clinicians, using the ETRC questionnaire

#### Secondary outcome measures

-To explore perceptions of HRQoL) among PWEs and their families using PedsQL scores.-To assess behavioral and emotional functioning using YSR/ASR and CBCL/ABCL questionnaires.-To explore associations between ETRC scores and patients’ clinical characteristics, HRQoL, and comorbidities in relation to transition readiness, and to identify individuals at higher risk of poor transition outcomes who may benefit from targeted social or psychoeducational interventions.

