## Background

Epilepsy is a neurological disease characterized by an enduring predisposition to generate epileptic seizures and often carries neurobiological, cognitive, psychological, and social consequences [1]. It is a common neurological condition in childhood, with an incidence of 5–7 cases per 10,000 children and adolescents [2]. Many childhood-onset epilepsy cases do not achieve remission in adulthood [3], thus necessitating a transfer from pediatric to adult epileptology [4]. This transfer, however, goes beyond a simple "handover" of care; it involves a well-coordinated process addressing the medical, psychosocial, and psychoeducational needs of patients with epilepsy (PWE) and their families [5].

Transition is a structured process that supports adolescents and young adults with chronic conditions in moving from child-centered to adult-oriented healthcare systems, ensuring continuity of care while addressing medical and psychosocial needs. Unlike the transfer of care, which represents a single event, transition is a gradual and dynamic process requiring preparation, patient engagement, and coordination between healthcare providers. The primary aim of the transition process is to minimise the risk of clinical deterioration, suboptimal treatment adherence, and loss to follow-up, all of which may substantially compromise the quality of life of patients and their families [6]. Well-organized transition pathways have been associated with improved long-term outcomes and better patient engagement. When inadequately managed, this phase may lead to poor adherence and loss to follow-up, with potential negative consequences on clinical outcomes [5].

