#### Measures

During the last evaluation at the Child Neuropsychiatry Unit (T0), subjects will complete the Italian version of the following tools:•Patient-Reported Questionnaires:- Epilepsy Transition Readiness Checklist (ETRC) [11]- Pediatric Quality of Life Inventory - Teen version (PedsQL 4.0) [12]- Youth Self-Report (YSR/11–18) [13]•Caregiver-Reported Questionnaires:- Child Behavior Checklist (CBCL/6–18) [14]- Caregiver versions of the ETRC and the PedsQL.•Pediatric Neurologist-Reported Questionnaire:- Screening Transition NEEDS Questionnaire (see Supplementary material3)

During appointments at the Adult Epileptology Service (T1 and T2), participants and caregivers will complete assessments as follows:•T1 Visit:- Participants and Caregivers: PedsQL, ETRC, and Qualitative EPI-STEP Questionnaire version A (see Supplementary material 4)•T2 Visit:- Participants and Caregivers: PedsQL, ETRC, Adult Behavior Checklist (ABCL) [13], Adult Self-Report (ASR) [13] and Qualitative Epi-STEP Questionnaire version B (see Supplementary material 4)

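### The secondary aim of finding patients at risk of a poor transition has no stated outcome that measures a poor transition; the planned analysis can find only correlates of low readiness

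*Protocol article*

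**What the plan says.** The third secondary objective has two halves. The first is "To explore associations between ETRC scores and patients’ clinical characteristics, HRQoL, and comorbidities in relation to transition readiness". The second is "to identify individuals at higher risk of poor transition outcomes who may benefit from targeted social or psychoeducational interventions". The article does not say what counts as a poor transition outcome.

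The Background describes what transition is meant to achieve: to "minimise the risk of clinical deterioration, suboptimal treatment adherence, and loss to follow-up". It adds that, badly managed, "this phase may lead to poor adherence and loss to follow-up, with potential negative consequences on clinical outcomes".

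The listed outcomes are as follows.

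- **Primary:** readiness, "defined as the preparedness to manage healthcare needs, treatment adherence, and communication with clinicians, using the ETRC questionnaire".
- **Secondary:** quality of life "among PWEs and their families using PedsQL scores", and "To assess behavioral and emotional functioning using YSR/ASR and CBCL/ABCL questionnaires".

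The Measures section gives the T1 content as "Participants and Caregivers: PedsQL, ETRC, and Qualitative EPI-STEP Questionnaire version A". T2 repeats PedsQL and ETRC and adds ABCL, ASR and version B of the qualitative questionnaire. The Statistical analysis section plans comparisons of these scores over time, and correlations of ETRC scores with clinical, demographic and psychosocial variables.

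**The concern.** To identify people at higher risk of an event, a study needs a variable that records the event and an analysis that relates candidate predictors to it. The stated outcomes and analyses supply neither. If the study is run as written, a patient with a low ETRC score may be reported as high risk although nobody has checked whether such patients miss treatment, fall out of care or worsen more often than others.

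The consequence is practical. The clause would steer social and psychoeducational support to the people so labelled, and the abstract expects the findings to guide interventions that improve clinical outcomes. That use assumes a link between readiness and later outcome, which is the link the aim needs tested.

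**Working it through.** This is a comparison of a stated aim with stated outcomes. Arithmetic enters only in costing the fix.

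**Step 1: each harm in the Background against the outcome lists.**

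- *Clinical deterioration.* No seizure or clinical-course outcome is listed. PedsQL, ASR and ABCL could show a decline in quality of life or in emotional and behavioural state, but the protocol does not call such a decline a poor transition outcome.
- *Adherence.* No outcome records whether treatment was taken. The ETRC touches on it. Under Assessment tools overview it covers how able and ready the patient is to manage medication, and its upper response options ask whether the patient has started doing something or always does it. It therefore partly reflects self-reported practice, but it is scored and defined as preparedness.
- *Loss to follow-up.* No attendance or retention outcome is listed at T1 or T2. The exclusion criteria also remove those who choose to be followed elsewhere, which takes out one route of loss from the centre.

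Result: 0 of 3 harms is a listed outcome.

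**Step 2: other T2 information.** The T2 contact covers the experience of transfer, and version B of the qualitative questionnaire adds one satisfaction question. Neither is named as an outcome.

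**Step 3: the association analysis.** It has the ETRC on one side and patient variables on the other. A correlation there shows which features go with low or high readiness. Because no transition outcome is on either side, it cannot show which patients go on to a poor transition.

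**Step 4: what 90 participants could support if an outcome were added.** The plan's own precision figure comes first. With z = 1.96, expected readiness p = 0.70 and n = 90 (Sample size calculation), the half-width of the 95% interval is

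1.96 × √(0.70 × 0.30 / 90) = 0.0947,

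which agrees with the stated 9% after rounding. This concerns the readiness proportion only, and the point does not depend on it.

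The document gives no rate of poor outcome, so the following rates are assumptions. The same formula, with all 90 observed, gives:

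- 10%: 0.10 × 90 = 9 events; half-width 1.96 × √(0.10 × 0.90 / 90) = 0.062
- 20%: 0.20 × 90 = 18 events; half-width 1.96 × √(0.20 × 0.80 / 90) = 0.083
- 30%: 0.30 × 90 = 27 events; half-width 1.96 × √(0.30 × 0.70 / 90) = 0.095

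A rate could be described to within about 6 to 9 percentage points. With 9 to 27 events, associations with T0 scores would be imprecise and could only be exploratory.

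**The case against.** The best defence is that the three harms come from a general account of what transition is for, not from the study's own objectives. The objectives at the end of the Background are readiness, quality of life, behaviour and unmet needs, and they close on factors associated with readiness. On that reading the disputed clause is half of one exploratory bullet and means only that patients with low readiness will be flagged for support, which the planned correlations can do. This stands in part. The document never equates poor transition outcomes with the three harms; they are used here because they are the only account it gives of a transition going wrong. But if low readiness is what is meant, the clause should say so, since it now claims risk of an outcome.

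A second defence is that the case report form and the full protocol are not shown and may hold clinical-course or attendance fields. They may. But the article lists its outcomes and its association analysis, and neither uses such a field. The gap is between an aim and outcomes that are both stated, which differs from detail left to another document.

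Some stronger readings are tempting but not supported:

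- A reader might infer that the ETRC is related only to baseline features. The text fixes no timing for the clinical variables, and PedsQL is collected at T0, T1 and T2.
- A reader might infer that patients go unobserved during transfer. They are assessed at T1, with paediatric and adult neurologists both present, and contacted again at T2. What is missing is a stated outcome, not contact.
- A reader might infer that a safety question goes unanswered. The study is observational and poses none.
- A reader might infer that adherence is wholly absent. The ETRC response options capture some reported practice.

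**Conclusion.** The point holds as a mismatch between one stated secondary aim and the stated outcomes. None of the three harms in the Background is a listed outcome, the term in the aim is undefined, and the one association analysis contains no transition outcome. The study as written can identify correlates of low readiness; it cannot support a conclusion about risk of poor transition.

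The reach is limited. The primary outcome, the score changes over time and the correlations themselves remain valid for what they measure. The conclusion assumes that the outcome lists in the article are complete. If the full protocol defines a poor transition outcome and an analysis of it, the article only needs to state them. The plan should be corrected before results are interpreted as risk, but this is no reason to doubt the primary analysis.

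**What to change.** Choose one of two changes.

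**Option A: give the aim an outcome.** Define a poor transition outcome from contacts already planned:

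- unplanned non-attendance at T1, or no contact at T2. Count separately any transfer that the clinician postponed after the NEEDS screening, so that a planned delay is not recorded as a harm;
- missed treatment reported by the patient or caregiver at T1 and T2;
- clinical worsening since the previous study visit, with a written definition, recorded where a neurologist sees the patient: at T1, and at T2 if that contact is in person. T2 may be a telephone interview, so this item will be incomplete, and the number assessed should be reported.

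Report each component with a 95% confidence interval, and relate T0 ETRC and T0 NEEDS scores to each in analyses labelled exploratory. The cost is a few case report form fields, short questions at T1 and T2, and a brief descriptive analysis. The drawback is the imprecision shown above.

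**Option B: narrow the aim.** Reword the clause so that it speaks of identifying individuals with lower transition readiness, and draw no conclusion about risk of poor outcomes. This costs one sentence and needs no new data, but gives up the risk question.

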### Statistical analysis

To address the primary outcome, transition readiness (ETRC scores) will be evaluated longitudinally across T0, T1, and T2. The proportion of ready subjects will be reported at each timepoint. Changes in ETRC scores over time will be analyzed using repeated measures ANOVA. Pairwise comparisons between timepoints (T0 vs T1, T0 vs T2, T1 vs T2) will be performed using paired t-tests or non-parametric equivalents where appropriate. To investigate secondary outcomes, changes in HRQoL (PedsQL scores) will be analyzed across T0, T1, and T2. Behavioral and emotional outcomes (YSR/ASR and CBCL/ABCL) will be compared between T0 and T2 using paired t-tests or non-parametric equivalents where appropriate.Associations between ETRC scores and clinical, demographic, and psychosocial variables will be explored using appropriate correlation analyses.The significance level will be set at 5%.

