### Procedures

The estimated total duration of the study is 48 months, of which 36 months will be employed in participants’ recruitment and minimum follow-ups will be organized after 12 months.

To evaluate the effectiveness of the transition process for both PWEs and their caregivers, data will be collected on the last visit at the Child Neuropsychiatry Unit (T0), on the first evaluation at the Adult Epileptology Service (T1) - usually between 6 and 18 months depending on the clinical needs of the PWEs - and on a 12-month follow-up appointment (T2). Study data will be collected in pseudo-anonymised form in an appropriate Case Report Forms (CRF; see Supplementary material 1), designed ad hoc and developed in compliance with good clinical practice (GCP) guidelines.

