#### T2-Follow-up transition appointment

Around 12 months (T2) after the first transition assessment, the PWEs/caregivers are further interviewed in person or by telephone regarding their transfer experience.

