#### Assessment tools overview

**Screening Transition NEEDS Questionnaire** (see Supplementary material 3): to provide a comprehensive understanding of the factors influencing transition readiness and to identify potential barriers, the Screening Transition NEEDS Questionnaire was developed. This tool, grounded in clinical and theoretical literature, offers a systematic and practical method for evaluating the complex needs of patients transitioning from pediatric to adult epilepsy care. The clinician completes five subsequent items assessing five crucial domains in the transition process (diagnostic, therapeutic, social, educational and emotional issues). Each question from A1 to A5 is worth 20% in the case of a negative response (“No”), while a positive response (“Yes”) corresponds to a score of 0%. A higher score indicates a greater degree of readiness. A score of 100% indicates that there are no gaps and so that the patient is fully ready for the transition. The cut-off score on the questionnaire is set at 60%. If a patient scores below this threshold, it suggests that there are critical aspects that need to be addressed before proceeding with the transfer. During the clinical visit, if the clinician identifies significant deficiencies in any domain (scores between 60% and 80%), appropriate interventions or recommendations will be made to address those areas. For instance, if a patient is undergoing psychodiagnostic evaluation due to a psychiatric comorbidity, and this aspect is not yet resolved, the clinician may identify a gap in the psychological/emotional domain and decide to delay the transition. Similarly, if there has been a recent change in the therapeutic regimen that requires follow-up, the therapeutic domain may need further attention before transitioning to adult care. At the end of this evaluation, a final question (question B) assesses whether the clinician believes that the patient and their family are ready for the transfer to adult neurology. Question B has two response options, “Yes” or “No”. The former response represents 100%, indicating readiness for the transition, while the latter corresponds to 0%, meaning that there are gaps that still need to be addressed, resulting in a postponement of the transition.

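### Repeated measures ANOVA and paired tests suit the ETRC visits poorly: complete sets will be fewer than 90, incompleteness may relate to readiness, and T0-T1 timing varies threefold

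*Protocol article*

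**What the plan says.** The Statistical analysis section sets three analyses of the ETRC over T0, T1 and T2:

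- a proportion: "The proportion of ready subjects will be reported at each timepoint";
- a test of change: "Changes in ETRC scores over time will be analyzed using repeated measures ANOVA";
- three pairwise comparisons, which "will be performed using paired t-tests or non-parametric equivalents where appropriate".

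On the error rate it says "The significance level will be set at 5"%. It does not say whether the pairwise tests depend on the ANOVA result.

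Other sections determine who has which visit, and when:

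- Procedures places T1 after T0 "usually between 6 and 18 months depending on the clinical needs of the PWEs". It gives a total duration of 48 months, 36 of them for recruitment.
- The T2 section places T2 "Around 12 months (T2) after the first transition assessment".
- The T1 section has the appointment arranged once the indication for transition is confirmed.
- Assessment tools overview describes the clinician-completed NEEDS screen. A score under 60% flags matters to settle before transfer. A negative answer to question B is described as "meaning that there are gaps that still need to be addressed, resulting in a postponement of the transition".
- The sample size section plans at least 90 participants and allows only for refused consent, not for missed visits.

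**The concern.** The named methods assume that nearly everyone has every visit and that a visit means the same elapsed time for each person. This design makes both doubtful.

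T1 depends on a readiness judgment in a study whose primary outcome is readiness. Its timing depends on clinical need. T2 comes a further year later, while the calendar leaves only 12 months after recruitment closes. Standard repeated measures ANOVA would discard T0 and T1 scores already collected from anyone without T2. The proportion ready at each visit could rest on a different group each time. The result would then describe those who moved through the pathway rather than those who entered it, and change over 6 months in some would be averaged with change over 18 months in others.

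**Working it through.** **1. The plan's own figure.** With 90 participants and 70% ready, the 95% half-width is 1.96 × √(0.7 × 0.3 / 90) = 9.47% (Wilson: 9.31%). Both agree with the stated 9%, but only if all 90 are measured at that visit.

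**2. Calendar.** T2 falls 6 + 12 = 18 to 18 + 12 = 30 months after T0. A participant reaches T2 by month 48 only if enrolled by month 48 − (T0-T1 gap) − 12. Assuming uniform entry over 36 months, no dropout and no visits after month 48:

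| T0-T1 gap | Latest enrolment month | Share reaching T2 | Of 90 | Half-width at 70% |
|---|---|---|---|---|
| 6 months | 30 | 30/36 = 83% | 75 | 10.4% |
| 12 months | 24 | 24/36 = 67% | 60 | 11.6% |
| 18 months | 18 | 18/36 = 50% | 45 | 13.4% |

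The last column is 1.96 × √(0.21/n). So 17% to 50% lack T2 from timing alone. Because the gap follows clinical need, the shortfall is larger among those seen later.

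**3. Illustration of selection on T0 readiness.** All inputs here are assumptions, since the article gives none. Scores are standardised with no true change and 70% ready at every visit. The correlation is 0.6 between T0 and T1. The chance of having later visits is logistic in the T0 score (intercept 0.75, slope 0.9 per SD), which keeps 65.5%, so about one third are lost.

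- Mean T0 score among those kept: 0.267 SD.
- Their mean T1 score: 0.6 × 0.267 = 0.160 SD, so the level at T1 is too high.
- Their change: 0.160 − 0.267 = −0.107 SD, about −0.11, although the truth is 0.
- Their proportion ready at T1: about 76% against a true 70%.

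The level and the change are thus biased in opposite directions. Completers start high and regress towards the mean.

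**4. Sensitivity to the assumptions.** Suppose instead that 25% to 100% of those not ready at T0 lack T1 and T2, with between-visit correlations of 0.3 to 0.7. Then 83 down to 63 of 90 remain. The proportion ready at T1 and T2 is 71% to 84%, and completers' T0-T1 change is −0.03 to −0.35 SD. If one third are lost at random, the proportion stays at 70% and the change at 0.

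**5. Pairwise tests.** With no true change, n = 90 and correlation 0.5, three ungated 5% tests give a family-wise error of about 12%. If they are run only after a significant ANOVA, it is about 5%. The article does not say which applies.

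**The case against.** A reader might infer that not-ready patients are lost by design and that readiness at T1 and T2 must therefore be biased upward. The documents do not support that.

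- The text speaks of postponement, and a postponed patient may still reach T1 later. The Background's aim to "minimise the risk of clinical deterioration, suboptimal treatment adherence, and loss to follow-up" describes transition in general, not expected attrition in this study.
- The gate is the clinician's NEEDS screen and question B, not the ETRC. Their correlation is not stated, so outcome-related missingness is plausible but not shown.
- Paired tests keep every available pair, so the loss to complete triplets applies to the ANOVA alone.
- Upward bias fits the level and the proportion, not the change analysis. There the illustration runs downward, and it could run upward if T1 were held back until a patient had become ready.
- Running out of calendar time need not depend on readiness, and the duration is given as an estimate.
- The 12% error rate holds only if the pairwise tests are ungated.

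All of this stands. It can also be said that missing-data rules usually belong in an analysis plan, which is not shown, and that the sample size section calls the primary outcome purely descriptive. That is fair as to detail. But the article does name the method, and the mismatch with the visit structure follows from its own timetable and gate.

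**Conclusion.** The point holds in limited form. The stated ANOVA and paired tests are a poor match for visits that are readiness-gated, irregularly timed and partly beyond the study calendar. The firmest part is the loss of complete sets: 17% to 50% without T2, given uniform entry and closure at month 48.

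The bias is conditional. If those less ready at T0 more often lack later visits, readiness at T1 would be overstated by about 6 percentage points (76% against 70%, one third lost), compared with a planned precision of 9. Completers' change would be understated by about 0.11 SD. Both figures rest on assumed correlations and an assumed loss mechanism. The true size depends on how closely the NEEDS screen tracks the ETRC, and it could be near zero.

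This is a cheap improvement to make before analysis, not a flaw that invalidates the study.

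**What to change.** Reword the Statistical analysis section as follows.

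- **Main model.** Replace the ANOVA and paired tests for ETRC by one linear mixed model (REML, unstructured within-person covariance) with visit as a factor, using every enrolled participant with at least one ETRC. Use the same model for PedsQL.
- **Pairwise contrasts.** Take them from this model, and only if the overall visit test is significant. With three visits this holds the family-wise error at about 5%.
- **Timing.** Add a supporting model with actual time since T0 (0 at T0) in place of nominal visit. Do not enter the T0-T1 interval as a main effect: it is undefined for anyone without T1, and it would shift all visits equally rather than adjust change.
- **Proportion ready.** Estimate it from a matching model averaged to the population level, or by multiple imputation.
- **Reporting.** At each visit give the denominator and the numbers postponed, not yet due and lost. State whether the exclusion of those leaving the centre applies only at entry.

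The cost is wording and somewhat more modelling in standard software, with no new measurements. The mixed model removes the bias only if missingness depends on observed data, such as the T0 ETRC, so a sensitivity analysis for departures from missing at random should accompany it.

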## Description of protocol

This is a monocentric observational study approved by our local Ethics Committee (approval code 2023–3.11/173) and registered at https://clinicaltrials.gov (code NCT06778772) on 16th January 2025. Prior participation, patients and caregivers will be fully informed about the study procedure and will be required to sign a written informed consent.

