**Qualitative Epi-STEP Questionnaire** (see Supplementary material 4): explores timing and introduction to the transition process, quality of information provided, expectations from adult neurology care and concerns about continuity of care and autonomy, with parallel patient and caregiver versions. This tool includes two versions: Version A, completed at T1, and Version B, completed at T2. Both assess the same domains, except that Version A is completed at the beginning of the transition process, while Version B is filled when the patient is already under the care of adult services and contains an additional question to assess the overall level of satisfaction with the transition process. This tool, grounded in clinical and theoretical literature, offers a systematic and practical method for evaluating the complex needs of patients transitioning from pediatric to adult epilepsy care.

**YSR/11–18** (Youth Self-Report) and **ASR** (Adult Self-Report): evaluate adaptive functioning, behavioral/emotional problems and social competencies, the former in teenagers, the latter in adults. Since participants are still under 18 at the beginning of the transition process, at T0 they complete the YSR/11–18, while at T2 they fill out the ASR.

**CBCL/6–18** (Child Behavior Checklist) **and ABCL** (Adult Behavior Checklist): caregiver reports providing insight into the individual's behavior and emotional state. The CBCL/6–18 is a parallel version of the YSR/11–18 and is given at T0, the ABCL is the parallel version of the ASR and is handed at T2.

**PedsQL** (Pediatric Quality of Life Inventory): assesses health-related quality of life (HRQoL) across physical, emotional, and social domains, with parallel patient and caregiver versions. According to the patient's age, the appropriate version will be administered, either the Teen (age 13–18) or the Young adult (age 18–25) version [12].

**ETRC** (Epilepsy Transition Readiness Checklist): explores the patient’s readiness for the transition process in 16–17-year-old teenagers, with parallel patient and caregiver versions. This checklist investigates to which extent the patient is capable and ready to manage healthcare issues, compliance to pharmacological therapy and communication with clinicians. These measures provide a structured framework for evaluating transition readiness and identifying barriers to successful transitions from pediatric to adult epilepsy care.

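### The T0–T2 paired test of YSR against ASR and CBCL against ABCL cannot separate change over time from change of form, and the article names no common score metric or caution

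*Protocol article*

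**What the plan says.** The Secondary outcome measures section sets the aim: "To assess behavioral and emotional functioning using YSR/ASR and CBCL/ABCL questionnaires". The Statistical analysis section gives the method: "Behavioral and emotional outcomes (YSR/ASR and CBCL/ABCL) will be compared between T0 and T2 using paired t-tests", or non-parametric equivalents.

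The Assessment tools overview fixes which form is used when. For self-report, "at T0 they complete the YSR/11–18, while at T2 they fill out the ASR". It describes these two forms as intended "the former in teenagers, the latter in adults". For caregivers, "The CBCL/6–18 is a parallel version of the YSR/11–18 and is given at T0", and "the ABCL is the parallel version of the ASR and is handed at T2". The Measures section agrees: YSR and CBCL at T0, ASR and ABCL at T2, and no behavioural form at T1.

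The design is single-group: "This is a monocentric observational study approved by our local Ethics Committee". The Limitations section reports none.

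**The concern.** A paired test assumes that the two values being subtracted lie on the same scale. Here no participant completes the same behavioural form twice, so the within-person difference mixes two things: how the person changed, and how the adult form scores relative to the youth form.

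The article calls forms parallel only across informants, CBCL with YSR and ABCL with ASR. It does not say that a youth-form score and an adult-form score are interchangeable.

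This paired comparison is the only analysis named for change in this outcome. The Procedures and Protocol validation sections say that the data serve to judge how well the transition process works, and the latter includes psychosocial well-being. A difference produced partly or wholly by the change of form could then be reported as improvement or deterioration during transition.

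**Working it through.** **Inputs from the article**
- Forms: YSR and CBCL at T0 only, ASR and ABCL at T2 only (Measures; Assessment tools overview).
- Test: paired t-test or non-parametric equivalent, significance level 5% (Statistical analysis). Two-sided is assumed, since sidedness is not stated.
- Planned minimum: 90 participants (Sample size calculation).

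The article gives no sample-size figure for the behavioural outcomes. Its one precision figure concerns the primary outcome and reproduces: 1.96 × √(0.7 × 0.3 / 90) = 0.0947, which rounds to the stated 9%. It is used here only as the source of n = 90.

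**Step 1: what is estimated.** For participant *i*, D_i = (true change)_i + (form difference)_i. The mean of D_i estimates the sum of the two averages. A signed-rank test uses the same D_i and has the same target.

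**Step 2: can the two be separated?** Take a model with intercept, time and form. Each T0 row is (1, 0, 0) and each T2 row is (1, 1, 1). The time and form columns are identical, so the matrix for 90 participants has rank 2 with 3 parameters. Adding participants repeats the same rows and leaves the rank at 2.

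**Step 3: how much could it matter?** The article gives no form offset, so a range is assumed. Let true change be zero and let the offset be *d* SDs of the paired differences. The noncentrality is *d*√n, with n − 1 = 89 degrees of freedom.

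| Assumed offset *d* | *d*√90 | Rejection, 90 pairs |
|---|---|---|
| 0 | 0 | 5% |
| 0.1 | 0.95 | about 15% |
| 0.2 | 1.90 | about 47% |
| 0.3 | 2.85 | about 80% |

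With 70 complete pairs, the last three rows become about 13%, 38% and 70%.

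The SD of the differences equals the SD of a single score when the within-person correlation is 0.5. If the offset is instead expressed in single-score SDs and the correlation is 0.7, it is divided by √(2 × 0.3) = 0.775. Offsets of 0.1, 0.2 and 0.3 then give about 23%, 68% and 95% with 90 pairs.

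**Step 4: the age assumption.** The Assessment tools overview says that participants are under 18 when transition begins. The Participants section sets only a minimum age of 16. Anyone over 18 at T0 would be given a youth form outside its labelled range. T0 to T1 is usually 6 to 18 months and T1 to T2 about 12, so T0 to T2 is about 18 to 30 months. Someone entering on their 16th birthday could be 16 + 1.5 = 17.5 years old when given the adult form.

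**The case against.** **The metric may be defined elsewhere.** The article does not say which scores will be compared. Scoring conventions commonly sit in the analysis plan or the case report form instructions, which are not shown and may already specify normed scores. This stands, and it rules out one tempting inference, that raw totals will be subtracted: nothing in the article says so. It does not dispose of the point, because the article itself states both the schedule and the test, and norming does not remove the aliasing.

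**The forms address the same construct.** The article describes YSR and ASR together as covering adaptive functioning, behavioural and emotional problems, and social competencies. That is fair, and calling them unrelated questionnaires would go too far. A shared construct still does not make the scores interchangeable.

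**The harm is hypothetical.** This also stands. The offsets are assumptions, and the range properly includes zero, where the test keeps its 5% level. A reader might infer that a spurious finding is likely, but the documents give no basis for any particular offset.

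**Some change of form is unavoidable as participants reach adulthood, and the outcome is secondary.** Both are true, and both limit the weight of the point. A description at each visit could also meet the stated aim.

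**Conclusion.** The point holds. With one form per visit for every participant, the planned T0–T2 difference is change plus form difference, and the design cannot split them. This conclusion rests on the article's own schedule and stated test and needs no numerical assumption.

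The size of the artefact is not known. The rejection rates of about 5% to 80% with 90 pairs depend on assumed offsets of 0 to 0.3 SD of the differences, no true change and a two-sided 5% test.

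A reader might also infer that participants who are already adult at T0 would yield an unconfounded estimate if given the adult forms twice. The documents do not support that. The article expects participants to be under 18 at the start, so this group may be very small or empty. Maturation over roughly 18 to 30 months would also remain in a study with no comparison group.

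The matter is worth correcting, but it is confined to a secondary outcome. The primary analysis uses the ETRC at all three visits and is untouched.

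**What to change.** 1. **Statistical analysis:** limit any T0–T2 comparison to age-normed standard scores on scales present in both the youth and adult forms, and name those scales. The article lists neither scales nor norms, so the sponsor must confirm which qualify. Make the proportion in the clinical range at each visit, with 95% CIs, the main description.
2. **Statistical analysis and Limitations:** state that T0–T2 differences include the change of form and will not be read as an effect of transition. Norming reduces the problem but does not remove it.
3. **Participants and Assessment tools overview:** reconcile the minimum age of 16, which has no upper limit, with the statement that participants are under 18 at the start. If adults can enter, give them the adult forms at both visits and report same-form change as a supportive analysis only.

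The cost is a few sentences, fewer comparable scales, a weaker conclusion about behavioural change, and a small change to the form schedule and case report form for adult entrants. If the full analysis plan already names a normed metric, the score choice in item 1 needs only a cross-reference. The clinical-range description and items 2 and 3 still apply.
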